## Abstract

**Background:**

Despite medical advances, major surgery remains high risk. Up to 44% of patients experience postoperative complications, which can have huge impacts for patients and the healthcare system. Early recognition of postoperative complications is crucial in reducing morbidity and preventing long-term disability. The current standard of care is intermittent manual vital signs monitoring, but new wearable remote monitors offer the benefits of continuous vital signs monitoring without limiting the patient’s mobility. The aim of this study is to evaluate the feasibility, acceptability and clinical impacts of continuous remote monitoring after major surgery.

**Methods:**

The study is a randomised, controlled, unblinded, parallel group, feasibility trial. Adult patients undergoing elective major surgery will be invited to participate if they have the capacity to provided informed, written consent and do not have a cardiac pacemaker or an allergy to adhesives. Participants will be randomly assigned to receive continuous remote monitoring and normal National Early Warning Score (NEWS) monitoring (intervention group) or normal NEWS monitoring alone (control group). Continuous remote monitoring will be achieved using the SensiumVitals® wireless patch which is worn on the patient’s chest and monitors heart rate, respiratory rate and temperature continuously and alerts the nurse when there is deviation from pre-set physiological norms. Participants will be followed up throughout their hospital admission and for 30 days after discharge. Feasibility will be assessed by evaluating recruitment rate, adherence to protocol and randomisation, and the amount of missing data. The acceptability of the patch to nursing staff and patients will be assessed using questionnaires and interviews. Clinical outcomes will include time to antibiotics in cases of sepsis, length of hospital stay, number of critical care admissions and rate of readmission within 30 days of discharge.

**Discussion:**

Early detection and treatment of complications minimises the need for critical care, improves patient outcomes, and produces significant cost savings for the healthcare system. Remote continuous monitoring systems have the potential to allow earlier detection of complications, but evidence from the literature is mixed. Demonstrating significant benefit over intermittent monitoring to offset the practical and economic implications of continuous monitoring requires well-controlled studies in high-risk populations to demonstrate significant differences in clinical outcomes; this feasibility trial seeks to provide evidence of how best to conduct such a confirmatory trial.

**Trial registration:**

This study is listed on the ISRCTN registry with study ID ISRCTN16601772.

## Background

Patients having major surgery are at high risk of complications, some of which can be life-threatening. Rates of complications have been found to be as high as 33–44% in patients undergoing surgery for gastrointestinal cancers [1]. Patients who develop postoperative complications become progressively unwell, often over a short period of time. Early recognition of postoperative complications is crucial in reducing morbidity and preventing long term-disability; for patients with septic shock, there is an 8% increase in mortality for every hour of delay in antibiotic administration [2].

The more unwell a patient becomes, the more likely they are to require higher level care, on either high-dependency units (HDU; level II) or intensive care units (ICU; level III). Escalation of care comes at significant cost to both the patient and the health service and is associated with worse patient outcomes. The average cost of a level I (general ward) bed is £433/day, as compared to £1033/day for a HDU bed, and £1351/day for an intensive care bed [3]. Early detection and treatment of complications minimises the need for level II/III care, improves patient outcomes and produces significant cost savings.

One of the ways patients are monitored for complications is by recording on a chart their vital signs. The vital signs are used to form a score, the National Early Warning Score (NEWS), which can alert if the patient becomes unwell. The vital signs included in the NEWS score are blood pressure, heart rate, breathing rate, oxygen saturation, level of consciousness and temperature [4]. The NEWS score also takes into account the need for supplementary oxygen to maintain a patient’s saturations. Typically, in the postoperative period, NEWS will be calculated half hourly for the first few hours, and if the patient remains stable, the frequency will decrease to 2-hourly and then 4-hourly, until the patient is ready for discharge when the NEWS may be recorded only twice a day.

Although NEWS has proven benefit, it suffers from several drawbacks. A 2012 study evaluated early warning scores in patients 48 h before an adverse event [5]. Of patients, 81% had a score indicative of deterioration, but recordings were ‘mostly incomplete’ with respiratory rate documented in ‘only 30% to 66%’. NEWS relies on manual observations, is time-consuming, and open to user interpretation. Vital signs are taken at predetermined intervals (typically 4-hourly), with patient deterioration possible between recordings. It has been suggested that the gap between observations is one of the primary failings of the NEWS system [6].

A solution to the problem of inadequate monitoring frequency is continuous monitoring at the bedside. Continuous monitoring is used in level II/III care, but is limited by “hard-wired” equipment, which tethers the patient to the bed space. This hinders patient mobility and potentially slows their recovery. One study tested ICU-style monitoring on a general ward and found that only 16% of patients remained connected in a 72-h period [7].

A number of systems have been designed that combine the benefits of a wearable, wireless patch with continuous monitoring of vital signs. One such device is the SensiumVitals® which monitors heart rate, respiratory rate and temperature continuously. The data are transmitted wirelessly every 2 min to a mobile device carried by the nurse which alerts when there is deviation from pre-set physiological norms.

It is hypothesised that the remote continuous monitoring system, as an adjunct to standard NEWS monitoring, will allow earlier detection of postoperative complications. This should reduce morbidity, which in turn should result in a decreased need for high dependency/intensive care.

Studies evaluating continuous monitoring of multiple vital signs parameters have shown mixed results. There is a preponderance of observational studies, which means that causal associations between interventions and patient outcomes have to be interpreted with care. An industry-funded controlled before-and-after study of 7643 patients [8] found that continuous monitoring on a medical-surgical unit was associated with a decrease in total ICU days, but the rate of ICU admission was unchanged.

The three largest randomised controlled trials in this area show conflicting results but share common limitations. A randomised controlled trial of 402 high-risk medical and surgical patients found that continuous multi-parameter monitoring showed no effect on adverse events or mortality [9]. However, only 16% of the patients were continuously monitored for the full 72 h intended. Patient and staff compliance may have influenced the impact of the interventions. This trial was also underpowered to detect differences in clinical outcome measures given the complex nature of the intervention under investigation.

Demonstrating significant benefit over intermittent monitoring to offset the practical and economic implications of continuous monitoring is difficult and requires large, well-controlled studies in high-risk populations to demonstrate significant differences in clinical outcomes, such as critical care admissions. Given the complexity of the intervention, before a definitive trial is designed, there is the need for a feasibility study focussed not only on clinical outcome measures but also patient and nursing acceptability and compliance. Compliance is unpredictable yet crucial to the adequate assessment of the intervention. If the patient or nursing staff refuse to engage with the monitoring device, this will negate the need for a definitive trial. In addition, a feasibility study will allow the identification of barriers to recruitment and protocol adherence and allow optimisation of the trial design and the technology itself.

### Aims

The main aim is to determine the feasibility of performing a large-scale randomised controlled trial of continuous remote monitoring after major surgery. A secondary objective is to evaluate the safety, potential efficacy and acceptability of a wearable, remote monitoring system for patients after major surgery, as compared to standard monitoring with the NEWS system alone.

### Trial design

This is a single-centre, feasibility, randomised, controlled, parallel group trial of continuous remote vital signs monitoring for patients who have undergone major elective general surgery. Participants will be individually randomised on a 1:1 basis to receive either remote monitoring plus NEWS or monitoring by NEWS alone. Randomisation will use random permuted blocks and be stratified by ASA (American Society of Anaesthesiologists comorbidity score) and gender.

## Methods

### Study setting

All participants will be recruited from St James’s University Hospital, Leeds, UK.

### Inclusion criteria

Patients who are undergoing elective surgeryPatients who have the capacity to provide informed, written consent on admissionAll ages ≥ 18 years

### Exclusion criteria

Patients who have undergone emergency surgeryAllergy to adhesives on electrodesCardiac pacemaker in situ

### Recruitment

Patients will be selected on the basis that they are undergoing elective major abdominal surgery and are anticipated to return to one of the participating wards afterwards. Types of surgery can include, but are not limited to, colorectal, upper gastrointestinal, liver, pancreas and biliary surgeries.

Table 1 illustrates the participant timeline for this study. Patients will be identified, recruited and consented for inclusion in the trial on the day of their surgery. This will take place on the General Surgical Admissions Lounge where patients attend on the morning of their elective procedures.

**Table 1 Tab1:**
[figure not shown]
Schedule of enrolment, interventions, and assessments

The patients will be given information in the form of a patient information sheet regarding the study. Following a period of consideration, if they consent to participate in the study, they will be randomised into one of two monitoring arms.

### Randomisation

Following confirmation of eligibility and written informed consent, participants will be randomised into the trial by an authorised member of staff at the research site. Randomisation will be performed centrally using the University of Leeds Clinical Trials Research Unit (CTRU) 24-h randomisation service, either via the telephone or the CTRU website.

Participants will be randomised on a 1:1 basis and will be allocated a unique trial number. Randomisation will be conducted using stratified block randomisation with variable block size with sex (male/female) and ASA grade (grades 1–4) as stratification factors.

The randomisation sequence will be provided by a statistician in the Leeds Clinical Trials Research Unit and computer generated using SAS 9.4 (SAS Institute Inc., USA, 2013). This sequence will be implemented and delivered by programmers through the Leeds CTRU Gen24 system, a dedicated telephone and web-based randomisation service.

### Interventions

Patients randomised to the ‘intervention’ arm will receive a patch and standard NEWS monitoring.

When the patient comes out of theatre, they are nursed in Recovery for a short time before being admitted on to the receiving ward. The patients allocated to receive the remote monitoring will, where possible, have the patch applied in Recovery by a member of the research team. If for any reason the patch cannot be applied in Recovery, it will be applied as soon as possible upon the patient’s return to one of the participating wards. If a participant is admitted to level II/III care after surgery and before returning to a participating ward, they will have the patch applied in Recovery but the patch will only be activated once the patient returns to the participating ward. This will usually be 1–2 days later.

Two colorectal surgery wards will be participating in the study: male and female. The male ward houses 25 beds, whilst the female ward houses 28 beds.

The patch will activate on arrival on the ward, and the patient’s nurse will carry a mobile device to alert them if the vital signs stray outside of normal parameters. Remote monitoring data will also be accessible on the ward computer screens for wider access. There will be no dedicated telemetry screen for the patch data.

Nursing staff will be provided with thorough training before the commencement of the study. This will involve training in the application and removal of the patch, the use of the mobile application and how to acknowledge alerts. If the mobile devices alert the nursing staff to abnormal vital signs, the ensuing clinical response is not mandated, but left to the nurse’s discretion.

In order to monitor alarm burden, the Clinical Fellow assigned to the trial will make daily ward visits and ask the nursing staff about false alerts. The Fellow will then adjust the monitor’s delays and thresholds on an individual basis and according to clinical need, for instance, adjusting the heart rate alert threshold in patients with pre-existing cardiac arrhythmias.

During these daily ward visits, the Fellow and the research nurse will also be responsible for changing expired patches and removing patches upon patient discharge. In order to optimise patient comfort and compliance with the device, it will also be possible to adjust or replace electrodes, including after patient washing.

Patients in the ‘control’ arm will receive standard NEWS monitoring alone. All usual nursing and medical care are permitted within both arms of the trial.

### Blinding

Blinding is not applicable for this study. Neither the patients nor the nursing staff can be blinded to the intervention received. The data collection will be performed by a research nurse and clinical fellow, who will both be administering the monitoring device, and so are necessarily unblinded. However, the objective methods of collecting the outcome data minimise the risk of bias. These data will be taken from the clinical records made by the patients’ usual care teams, including a succession of junior medical staff on rotation, who will be unaware of the study. In addition, the predefined criteria for the outcome measures provide minimal scope for interpretation of their presence or absence by the data collection team. The clinical fellow will be performing the analysis alongside an unblinded statistician.

### Data collection

The patients will remain in their allocated study arm for the duration of their hospital stay. If a remotely monitored patient is moved to a critical care bed during their admission, the remote monitoring will be temporarily suspended pending reinstatement depending whether they return to a participating ward. Every effort will be made to ensure that participants remain in the study arm to which they were originally allocated, and any non-compliance will be recorded.

Patients’ participation in the trial will end when they are discharged from hospital. At this point, remotely monitored patients will be invited to complete a questionnaire regarding their experiences of wearing the patch (see Appendix 1). Information regarding the admission will be collected once the patient has left hospital. Information will also be collected regarding the number of patients who agree to take part in the study, those who do not and the reason for not taking part.

The nursing staff (registered nurses and healthcare assistants) will be invited to complete a paper questionnaire about system usability (see Appendix 2). They will also be invited to undertake a semi-structured interview regarding their experience of providing the new monitoring system based on a purposive sampling strategy, to get the most comprehensive impression of nursing perceptions. This purposive sample will include nurses at various grades and with different experiences of the device.

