### Secondary outcome measures

Time to antibiotics in cases of sepsisNumber of HDU/ICU admissionsLength of stay in HDU/ICUTotal length of stay in hospitalNumber of postoperative complications, defined and scored according to the Clavien-Dindo classification of surgical complications [10]Number of reinterventions, defined and scored according to the Clavien-Dindo classification of surgical complications [10]Patient acceptability using questionnaire scoresNumber of patients not wearing patch for at least 5 daysNursing acceptability using questionnaire scores and thematic analysis of interviews30-day readmission rate

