### Planned analyses

Analyses have been pre-specified in a statistical analysis plan. The analysis of the primary and secondary outcome measures will take place when all participants have been followed up (i.e. 30 days after the last recruited participant’s date of discharge). No interim analyses are planned but safety data will be presented to the Multidisciplinary Advisory Group at regular intervals.

Analysis will be carried out following the principles of modified intention-to-treat (ITT). The modified ITT (mITT) population will include all participants randomised to the trial, analysed according to the treatment group to which they were randomised, regardless of adherence to the protocol. The mITT population will not include any participants who are classed as ‘drop-out’ due to design (i.e. those who were never admitted to a participating ward).

As this is a feasibility study, no formal comparison between the study arms will be undertaken. Summaries will be produced by subgroup to determine any differences between low- and high-risk patients. High-risk patients will be defined as ASA > 2 undergoing major + surgery or ASA = > 2 with a perioperative critical care admission.

Baseline characteristics will be summarised descriptively overall and by trial arm. No statistical comparison between trial arms will be made.

Quantitative secondary outcome measures will be summarised descriptively using appropriate summary statistics both overall and by trial arm (mean, standard deviation, range and median for continuous outcomes and frequency and percentages for categorical measures). Proportions of missing data will also be presented. Data from patients discharged before the 5 days has elapsed will be censored. Qualitative secondary outcomes including patient acceptability and nurse acceptability will be analysed using a thematic analysis approach.

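### The protocol article gives two end points for follow-up, discharge and 30 days after discharge, so the window for clinical event counts is unsettled; the analysis date can also leave a few long-stay patients incomplete

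*Protocol article*

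**What the plan says.** The protocol article describes the end of follow-up in four places.

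- **Data collection:** patients' "participation in the trial will end when they are discharged from hospital". The only clinical data collection described there is for the hospital stay: "Information regarding the admission will be collected once the patient has left hospital".
- **Abstract, Methods:** "Participants will be followed up throughout their hospital admission and for 30 days after discharge". The clinical outcomes listed there include the "rate of readmission within 30 days of discharge".
- **Secondary outcome measures:** 30-day readmission is listed. So are total length of stay, HDU/ICU admissions, postoperative complications and reinterventions. The event counts carry no time window, for example "Number of reinterventions, defined and scored according to the Clavien-Dindo classification of surgical complications".
- **Planned analyses:** the analysis takes place "when all participants have been followed up", which is then explained as "30 days after the last recruited participant’s date of discharge".

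Two further sections depend on where follow-up ends. Loss to follow-up is among the primary outcome measures, and the progression criteria limit missing data to 20% attrition.

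**The concern.** A patient whose participation stops at discharge cannot, on a plain reading, also be followed for the next 30 days. The choice matters in three ways.

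1. **Event window.** If follow-up stops at discharge, complications, reinterventions and critical care admissions are counted over a period equal to the length of stay. Length of stay is an outcome in its own right, and it could shift if the patch reduces morbidity as the Background hypothesises. Two arms with the same underlying risk would then show different counts.
2. **Attrition.** Loss to follow-up is close to zero by construction if follow-up ends at discharge. It is a real test if follow-up ends 30 days later. One of the two progression criteria rests on it.
3. **Analysis date.** The last participant recruited need not be the last to go home. Those still inside their 30 days on the stated date would be earlier recruits with long stays, so the gap is selective.

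The trial is meant to identify outcome measures and supply sample-size parameters for a definitive trial, so an unclear window would carry into that design.

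**Working it through.** **The plan's own figure.** Allowing for 20% going to non-participating wards, 120 / (1 − 0.20) = 150 randomised, as stated. Nothing here changes the sample size.

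**Event window.** The article gives no length of stay and no onset times, so these are assumptions:

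- a 30-day complication risk of 40% in both arms (the Background cites 33–44%);
- exponential onset times with mean m = 4, 6 or 8 days;
- stays of 8 days in one arm and 10 in the other, unrelated to onset.

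The proportion counted by day L is

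0.40 × (1 − exp(−L/m)) / (1 − exp(−30/m)).

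| m (days) | To discharge: L = 8 | To discharge: L = 10 | Difference (points) | To discharge + 30: difference, L = 38 v 40 (points) |
|---|---|---|---|---|
| 4 | 34.6% | 36.7% | 2.1 | 0.001 |
| 6 | 29.7% | 32.7% | 3.0 | 0.02 |
| 8 | 25.9% | 29.2% | 3.3 | 0.08 |

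For m = 6 and L = 8: 0.40 × (1 − exp(−1.333)) / (1 − exp(−5)) = 0.40 × 0.7364 / 0.9933 = 0.297.

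The dependence on stay is visible when counting to discharge and negligible when counting to 30 days after discharge. A fixed window from surgery removes it.

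For scale, the standard error of a difference between two arms of 60 is √(2 × p × (1 − p) / 60). This is 8.4 points at p = 0.30 and 8.7 points at p = 0.35.

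**Analysis date.** The two halves of the Planned analyses rule agree only if the last recruited participant is also the last discharged. This was simulated with 150 patients recruited uniformly over 365 days and lognormal stays (20,000 runs per setting). The stay distributions are assumptions.

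| Median stay (days) | Log-SD | Last recruited is not last discharged | Mean patients discharged later | Median delay to last discharge (days) | 90th percentile of delay (days) |
|---|---|---|---|---|---|
| 5 | 0.5 | 43% | 0.6 | 0.0 | 5.0 |
| 7 | 0.7 | 67% | 1.4 | 3.8 | 19.9 |
| 10 | 0.9 | 86% | 2.9 | 23.8 | 78.2 |

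The two wordings therefore often disagree, but over few patients: 1.4 of 150 on average in the middle case, and 0.6 to 2.9 across the nine settings run (medians 5, 7 and 10; log-SDs 0.5, 0.7 and 0.9).

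**The case against.** The strongest reply is that one sentence is loosely worded. It follows text about staying in the allocated arm during the hospital stay and leads into the discharge questionnaire, so it can be read as the end of monitoring and of the patient's active part. The Blinding section says that outcome data come from clinical records, and readmissions could be found there without further contact. Table 1, the schedule of assessments, is not available in the text reviewed and may settle the timing. This reading is plausible, but the article does not state it, and the Data collection sentence would still need correcting.

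It can also be said that a missing event window is a detail for the full protocol or the analysis plan. Taken alone, that is right. Here the end-of-participation sentence points to one window and the abstract to another, so what those documents would inherit is a contradiction rather than a gap.

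A reader might infer that the plan builds in an apparent benefit for the patch. The documents do not support that. No formal comparison of arms is planned. The 2 to 3 points arise only when counting to discharge, under an assumed two-day difference in stay, and are well below the standard error of 8 to 9 points. The calculation also ignores that complications themselves prolong stay.

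A reader might likewise infer that the analysis will be run on incomplete data. The governing clause requires everyone to have been followed up; only its explanation is imprecise. Nor do the documents show that death must be added as an outcome; that would be a preference.

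**Conclusion.** The contradiction over the end of follow-up stands. It leaves the window for complications, reinterventions and critical care admissions open, and with it the meaning of loss to follow-up and of the 20% attrition criterion. If the end is read as discharge, the event window moves with length of stay. If it is read as 30 days after discharge, that problem is negligible. The analysis-date wording is a smaller inconsistency, worth about 1 to 2 patients of 150.

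These sizes depend on assumed stays and onset times, because the article gives neither; the conflict in the text does not depend on them. The consequence is for descriptive event rates, attrition and the inputs to the definitive trial. It is a correction worth making, not a threat to an efficacy conclusion.

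**What to change.** 1. In Data collection, state that monitoring and the patient's active participation end at discharge, and that follow-up from clinical records ends 30 days after discharge, in line with the abstract and Planned analyses.
2. Count complications, reinterventions and critical care admissions over one fixed window from surgery in both arms, for example 30 days, whether the event occurs in hospital or afterwards. Keep readmission within 30 days of discharge as a separate outcome.
3. In Planned analyses, replace the last recruited participant's discharge with the last discharge of any participant, plus 30 days.

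The sample size does not change. Because discharge cannot precede surgery, follow-up to 30 days after discharge already covers 30 days from surgery. The costs are the changes of wording, case report form space to record and grade events after discharge, and a data cut that may fall some days later (median 3.8 days in the middle simulated case). Post-discharge events will be seen only where they reach the records, and the report should say so.
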